### Assessment of baseline balance and description of participants

We will calculate cluster-summaries for key sociodemographic characteristics of the sample recruited through RDS at both baseline and at endline, and report the cluster-mean and range for these, stratified by study arm. At baseline, we also estimate the level of inter-cluster variability in the primary outcome variable expressed in the form of the inter-cluster-pair coefficient of variation, known as k_m_ [8].

### Operationalising the primary outcome variable

All consenting women recruited to the RDS surveys will be tested for HIV antibody (laboratory analysis details below). Bloodspot samples from all women with detectable HIV antibody are then tested for viral load. For the analysis, those women who have ≥ 1000 copies/ml detected were categorised as having a detectable viral load. The primary outcome variable will be calculated as:$$ \begin{array}{l} = \mathrm{Number}\ \mathrm{of}\ \mathrm{women}\ \mathrm{with}\ ``\mathrm{detectable}"\ \mathrm{H}\mathrm{I}\mathrm{V}\ \mathrm{an}\mathrm{tibody}\ \mathrm{an}\mathrm{d}\ \mathrm{d}\mathrm{etectable}\ \mathrm{viral}\ \mathrm{load}/\\ {}\mathrm{All}\ \mathrm{women}\ \mathrm{who}\ \mathrm{had}\ \mathrm{an}\ \mathrm{H}\mathrm{I}\mathrm{V}\ \mathrm{an}\mathrm{tibody}\ \mathrm{test}\ \mathrm{performed}\end{array} $$

A range of secondary endpoints are described in the study protocol but are not discussed in detail here.

### Primary outcome analysis strategy

Our primary analysis will be a comparison of RDS-2 weighted, adjusted, endline cluster summaries of the primary outcome, adjusting for cluster summaries at baseline. We will then fit a linear regression model on the endline summaries, adjusting for the baseline cluster summaries and a dummy variable for the pair. We will calculate and report prevalence ratios and risk differences.

To address the possibility of confounding by individual and cluster-level variables from chance imbalances, we will conduct an adjusted analysis. This analysis will use the ‘two step’ method from Hayes and Moulton to adjust for differences in covariates at endline [15]. Potential confounders will be included that could affect the outcome but that are very unlikely to be on the causal pathway: education and age.

The two-step method will be applied to the endline cluster summaries. Step 1: For each site a logistic regression model will be fitted with the primary outcome as the dependent variable, and education, age, and pair as independent variables. This model will be used to ‘predict’ outcomes for each woman. To account for the sampling design, we will multiply the predicted values by the inverse of the degree (RDS-2), normalise for the cluster and calculate cluster summaries. Step 2: We will then divide the cluster summaries used in the unadjusted analysis (that is, accounting for RDS only) by the adjusted cluster summaries from Step 1 to generate ‘residuals’. We will calculate the effects using the regression model described above with the residuals as the dependent variable.

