### Sample size calculations

We enrolled 14 clusters in seven matched pairs in both the baseline and final RDS surveys, aiming to recruit 200 FSW at each site. We used the approach of Hayes and Bennett [8] to determine an appropriate sample size. RDS estimates can have high variance [9, 10], which translates to greater variation between cluster prevalence estimates in our analysis. Given the estimated prevalence of HIV and access to care at baseline, our estimate of intervention effect and the 14 clusters of approximately 200 FSW per site, we calculated that the matched-pair coefficient of variation could be up to k_m_ = 0.2, to achieve 80 % power ([name]: Antiretrovirals for HIV prevention and treatment among Zimbabwean sex workers, unpublished) (Fig. 2).

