**Fig. 2 Fig2:**
[figure not shown]
Sample size considerations for the SAPPH-IRe Trial. Notes: (**a**) We estimated that in the comparison arm 41 % of SW will have a detectable viral load at 24 months. The breakdown of hypothesised effect of the intervention on HIV prevalence, the proportion of HIV infected women who are diagnosed, the proportion of diagnosed women who are on ART, and the proportion of women on ART with detectable viral load is shown in Table 2. We hypothesize that with realistic estimates of the size of the potential effect of our intervention on improving knowledge of HIV status among HIV-infected SW, decreasing time to treatment initiation and improving adherence, in the enhanced intervention arm (Arm B) 28 % of SW should be expected to have detectable viral load at the time of the final RDS survey. We also show more ‘optimistic’ and ‘pessimistic’ scenarios. (**b**) Number of matched paired of SW clinics (clusters) and number of women per site required to detect a reduction in proportion of women not virally suppressed (not on ART or virologically failing) from 41 to 28 % (80 % power, 5 % level of significance) for various values of the between-cluster coefficient of variation (km) in the proportion not virally suppressed within matched pairs. (**c**) Power and between-cluster coefficient of variation (km) in the proportion not virally suppressed within matched pairs for different scenarios for realistic, optimistic and pessimistic hypothesised intervention effects with 7 pairs of matched pairs and 200 women per cluster (5 % level of significance)

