We recognise that there are potential limitations and threats to the research. The need to minimise contamination between communities has meant that we have only 14 clusters, which could make finding an effect challenging. While RDS weighting is intended to reduce bias in chain referral sampling, simulation and empirical studies have shown that variance around the weighted point estimates for each cluster could be very high [9, 10]. In our study, this variance will be reflected in the between-cluster differences. Our power calculations have accounted for a between-matched-pair coefficient of up to 0.19, and at baseline we calculated k_m_ to be 0.18 ([name], et al. HIV care cascade among female sex workers in Zimbabwe: baseline results of the SAPPH-IRe Trial, submitted). Additionally, we have sought to improve power by matching sites and adjusting our final analysis by baseline age and education characteristics.

While our aim of assessing the intervention under routine conditions makes recruiting a representative sample of FSW important, this is challenging when we lack a sample frame. We have sought to address this problem by using RDS, but we recognise that this is not a panacea in delivering unbiased representative estimates. Often RDS is implemented variably, limiting comparability. A strength of our study is the identical protocol implemented at each study site. We are aware of one other application of RDS in a cluster randomised trial, but to our knowledge no trials have yet been completed [34, 35]. We have described a range of potential biases that can arise from differences in the assumed and real sampling process under RDS. We have adapted our surveys to collect the information required to signal whether any of these biases could be present, and we have planned sensitivity analyses to assess their impact on our study findings.

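### The primary model standardises the endline cluster summary for age and education but not the baseline summary it adjusts for: no bias, probably a small loss of precision, and a fix that costs almost nothing

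*Protocol article*

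**What the plan says.** All of the following is in the protocol article.

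- **Primary analysis.** Primary outcome analysis strategy compares "RDS-2 weighted, adjusted, endline cluster summaries of the primary outcome", so the adjusted analysis is primary. The section on design features requiring special consideration makes the unadjusted analysis a sensitivity analysis.
- **Regression.** The endline summaries are modelled by linear regression, "adjusting for the baseline cluster summaries and a dummy variable for the pair".
- **Two-step adjustment.** "The two-step method will be applied to the endline cluster summaries". Step 1 predicts outcomes from education, age and pair. Step 2 divides the RDS-weighted summary by the predicted one, and this ratio becomes the dependent variable in the same regression.
- **Baseline covariate.** The Abstract (Methods) describes it as the cluster's baseline prevalence. No section gives it an age or education adjustment. RDS-2 weighting is the stated rule for cluster summaries in general (Analysis principles).
- **Data available.** The team will compute "cluster-summaries for key sociodemographic characteristics of the sample recruited through RDS at both baseline and at endline".
- **Timing of covariates.** The analysis section adjusts for covariates measured at endline. The Discussion says the final analysis is adjusted by age and education at baseline.

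**The concern.** The two sides of the primary regression are built differently. The endline ratio has had age and education mix divided out. The baseline summary still carries that mix, both lasting site differences and the chance composition of that RDS sample. Whatever part of a within-pair baseline difference is due to mix has nothing left to predict at endline and dilutes the covariate.

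What is at stake is precision. The Discussion concedes that 14 clusters may make an effect hard to find and presents covariate adjustment partly as a way to gain power, so an avoidable loss is worth removing even if it is small.

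**Working it through.** **1. How much slack the design has.** Inputs: "14 clusters of approximately 200 FSW per site" in 7 pairs; 41% against 28%; "80 % power, 5 % level of significance" (taken as two-sided). The Hayes-Bennett matched-pair formula is

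c = 2 + (1.96 + 0.84)² × [p0(1−p0)/m + p1(1−p1)/m + km²(p0² + p1²)] / (p0 − p1)².

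- Binomial part: (0.2419 + 0.2016)/200 = 0.00222.
- p0² + p1² = 0.1681 + 0.0784 = 0.2465; (p0 − p1)² = 0.0169.
- Setting c = 7 gives km = 0.186 for 80% power.
- Power is 82.1% at km = 0.18, 78.7% at 0.19 and 75.3% at 0.20.

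Sample size calculations states "matched-pair coefficient of variation could be up to k_m_ = 0.2, to achieve 80 % power"; the Discussion states "between-matched-pair coefficient of up to 0.19, and at baseline we calculated k_m_ to be 0.18". The 0.19 is reproduced to within 2 power points; 0.2 fits only as 0.186 rounded to one decimal. This does not test the present point. It shows only that there is little power to spare.

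**2. Degrees of freedom.** With arm in the model: 14 points − (1 intercept + 6 pair terms + 1 arm + 1 baseline term) = 5. Standardising the baseline term leaves this unchanged.

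**3. Algebra of the loss.** Let s be the share of within-pair baseline variance due to age/education mix, and R² the share of endline residual variance explained by a standardised baseline. If mix is unrelated to the standardised endline ratio, the unstandardised baseline explains R²(1 − s), and the standard error grows by the factor √{[1 − R²(1 − s)]/(1 − R²)}.

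| R² | s | R²(1 − s) | SE increase |
|---|---|---|---|
| 0.4 | 5% | 0.38 | 1.7% |
| 0.4 | 10% | 0.36 | 3.3% |
| 0.4 | 25% | 0.30 | 8.0% |
| 0.4 | 50% | 0.20 | 15.5% |
| 0.2 | 25% | 0.15 | 3.1% |
| 0.6 | 25% | 0.45 | 17.3% |

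The protocol gives neither R² nor s.

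**4. Simulation with inverse-degree weights.** 7 pairs, 200 women per site and survey, one pooled Step 1 model, 3,000 runs per row. Assumed: correlation of site effects over time 0.8, persistence of mix 0.8, between-site SD 0.3 on the logit scale. Log-odds coefficients for age and education were −0.3 and −0.4 (moderate) or −0.6 and −0.8 (strong).

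| Covariate effects | Spread of site mean age (SD) | Variance reduction kept by unstandardised baseline | SD of effect, unstandardised v standardised | Power, same order |
|---|---|---|---|---|
| moderate | 0.1 | 96% | +1.0% | 70.7 v 71.2% |
| moderate | 0.2 | 94% | +1.3% | 70.6 v 70.8% |
| moderate | 0.4 | 85% | +3.6% | 69.2 v 71.0% |
| strong | 0.1 | 89% | +2.3% | 67.9 v 69.5% |
| strong | 0.2 | 81% | +1.8% | 67.6 v 69.7% |
| strong | 0.4 | 59% | +8.4% | 62.6 v 67.3% |

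Shorter runs, which also tried a correlation of 0.5, gave a lower residual variance with the standardised baseline in every setting. In a few of them the SD of the effect was marginally higher (for example 0.1132 v 0.1117), which is compatible with simulation noise.

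**5. Other assumed settings.**

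- Log ratios, age only, odds ratio 1.5 to 1.8 per SD, site mean age varying by 0.2 to 0.35 SD, no RDS design effect, 1,500 runs: standardising the baseline cut the SD from 0.0978 to 0.0950 (3%), 0.0988 to 0.0928 (6%) and 0.1014 to 0.0918 (9%). Power rose by 2.1, 3.1 and 4.4 points.
- Similar odds ratios, mean-age spread 0.1 to 0.35 SD, 1,000 runs: SD reduction 1.5 to 3.3% at 200 women per site, −0.9 to 3.3% at an effective 100 (assumed design effect 2), and −0.4 to 2.2% at an effective 67.
- A further set with log ratios: about 2 to 4% with mild to moderate mix, 0.3 to 3% with RDS-type weights, and 7 to 10% only with strong effects and wide site differences.

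**The case against.** The strongest reply is that nothing here is wrong. Adjusting for cluster baseline prevalence is an ordinary, valid, pre-specified choice. A baseline covariate need not share the outcome's scale or be adjusted for the same factors. The size of the gain rests wholly on assumed inputs, pairing on setting and length of service may narrow differences in mix within pairs, and RDS variance shrinks the gain towards simulation error. A condensed article may also leave the construction of the baseline summary to the full plan.

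Most of this stands and limits the size of the point. Four stronger readings that a reader might infer are not supported:

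- **That the covariate loses much of its value.** In step 4 it keeps 81 to 96% of its variance reduction in all but the most extreme row.
- **That the baseline summary is crude.** RDS-2 weighting is the general rule; only the age/education adjustment is absent.
- **That mixing a prevalence with a ratio does harm.** The regression slope absorbs a linear rescaling.
- **That the effect estimate is biased.** The mismatch affects precision only.

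What the reply does not show is any drawback to treating both surveys alike. Nor is this merely an omitted detail: the article itself places the two-step method at endline and describes the covariate as baseline prevalence.

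**Conclusion.** The asymmetry is in the text and its expected effect is a loss of precision, but probably a small one: roughly 0 to 4% of the standard error and 0 to 2 power points under moderate assumptions. A loss near 10% and 5 points needs strong age and education effects together with large site differences in mix. The protocol reports no baseline-to-endline correlation, no covariate effects and no between-site spread, so no single figure can be given as this trial's loss.

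The simulations assume one pooled Step 1 model. Taken literally, a separate fit for each site cannot include pair, which is constant within a site. Some runs used log ratios, which the protocol does not mention. This is an optional improvement with a clarification attached, not a threat to validity.

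**What to change.** - Apply Step 1 and Step 2 to the baseline survey with the same covariates and RDS-2 weights. Enter the resulting baseline observed/expected ratio as the covariate in the adjusted primary model, on whatever scale the endline ratio is analysed.
- Keep the RDS-2 weighted baseline prevalence as the covariate in the unadjusted sensitivity analysis, and state explicitly how that summary is weighted.
- Reconcile the Discussion (age and education at baseline) with Primary outcome analysis strategy (covariates at endline).

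The cost is two or three sentences and a second run of the same code on data already collected. No degrees of freedom are lost. The change should be made before endline data are analysed.

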### Design features requiring special consideration in reporting and analysis

Our use of RDS to recruit participants creates several issues for analysis and reporting. We seek to apply the principles and practices of the CONSORT approach for cluster randomised trials, which maximise transparency in reporting [14]. However, some aspects of our design pose challenges in this respect. First, since no sample frame exists from which the research population has been systematically sampled, it is not possible to describe individual non-participation rates in the outcome surveys or to analyse whether these differ by study arm. This step is an important component in the reporting of trial profiles. We describe below the statistics that will be possible to report and consider the strengths and limitations of these. Second, analysing the potential for sampling bias in RDS-based samples from within-study clusters will be an important component of our analysis. Of particular importance for our trial will be to assess whether there is evidence that the operationalization of RDS has introduced systematic participant recruitment bias that differs by cluster, cluster pair, or trial arm. In the case of endline surveys, we will need to investigate whether recruitment patterns through RDS change over time because of either the previous application of RDS in the study clusters, or because of an effect of the intervention in the intervention arm. The intervention seeks to strengthen the social support and increase communication within the social networks of sex workers within each cluster. This intervention might plausibly also influence patterns of peer recruitment to the RDS-survey, and relevant statistics should be reported transparently within our analysis.

Finally, we must select a primary analysis approach suitable for the structure of our data. As described below, since we are conducting a cluster randomised trial with a relatively small number of clusters, we will use a cluster-summaries approach. Our primary analysis will be based on the two-stage approach of Hayes and Moulton [15] adapted for use with RDS. We will consider an unadjusted analysis as a sensitivity analysis. We describe our preferred approach in the next section, and consider the strengths and limitations in relation to alternatives in the discussion.

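### Step 1 of the primary analysis is written as a separate logistic model per site, which divides the intervention effect out of the residuals before it is estimated

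*Protocol article*

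**What the plan says.** The protocol article, section 'Primary outcome analysis strategy', sets out the adjusted analysis in two steps.

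- Step 1, model: "For each site a logistic regression model will be fitted with the primary outcome as the dependent variable, and education, age, and pair" as covariates. Study arm is not in the model.
- Step 1, prediction: "This model will be used to ‘predict’ outcomes for each woman". Then "we will multiply the predicted values by the inverse of the degree (RDS-2), normalise for the cluster and calculate cluster summaries".
- Step 2, residuals: the analyst will "divide the cluster summaries used in the unadjusted analysis (that is, accounting for RDS only) by the adjusted cluster summaries from Step 1".
- Step 2, effect: "We will calculate the effects using the regression model described above with the residuals as the dependent variable". That regression is linear and includes the baseline cluster summary and pair dummies. The article does not list an arm term, but one must be meant.

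The status of the analysis is set in 'Design features requiring special consideration in reporting and analysis'. The two-stage method is primary, and of the alternative it says: "We will consider an unadjusted analysis as a sensitivity analysis". Under 'Analysis principles', the conclusion depends on whether the 95% confidence interval for the prevalence ratio excludes 1. No section says that the Step 1 model is pooled across sites.

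**The concern.** The two-step method works because the Step 1 model predicts what each cluster's prevalence would be, given its covariate mix, if there were no intervention effect. For that, the model must span both arms and omit the arm term. An intervention cluster that does well then has fewer outcomes than predicted, and its ratio falls below that of its comparison pair.

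A model fitted to one site alone predicts that site's own result. The observed-to-expected ratio is then about the same in both arms whatever the intervention did, and Step 2 has nothing left to estimate. Because this is the primary analysis, the headline result would be close to no effect under true benefit or true harm.

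The sentence also conflicts with itself. All women in a site belong to the same pair, so pair cannot be estimated in a site-level model. An analyst must drop either the per-site fit or the pair covariate, and the two choices give opposite results.

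**Working it through.** **Inputs from the protocol article.** 14 clusters in 7 pairs, about 200 women per site ('Sample size calculations'). 41% versus 28% with the outcome, 80% power, 5% level (Fig. 2 legend). Matched-pair coefficient of variation k_m: up to 0.2 in 'Sample size calculations', up to 0.19 in the Discussion; 0.18 observed at baseline (Discussion).

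**Reproducing the plan's design figure (context only).** Hayes–Bennett matched formula, two-sided 5%:

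c = 2 + (1.96 + 0.842)² × [p0(1−p0)/m + p1(1−p1)/m + k_m²(p0² + p1²)] / (p0 − p1)²

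- At k_m = 0.18 the bracket is 0.2419/200 + 0.2016/200 + 0.0324 × 0.2465 = 0.01020. So c = 2 + 7.849 × 0.01020/0.0169 = 6.74 pairs, with 82.1% power at 7 pairs.
- Solving for 7 pairs and 80% power gives a maximum k_m of 0.186, which rounds to the 0.19 in the Discussion.

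The design inputs therefore hang together and can be used to test the analysis.

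**Algebra of a per-site fit.** For a logistic model with an intercept, the intercept's score equation is Σ(y − p̂) = 0 over the data fitted, so Σp̂ = Σy. In one simulated site of 200 women, Σy = 58 and Σp̂ = 58.0. With weights w = 1/degree, the Step 2 ratio is

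R = Σwy / Σwp̂ = 1 + Σw(y − p̂) / Σwp̂.

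- Unweighted: R = 1 exactly.
- Fit weighted by w: Σw(y − p̂) = 0, so R = 1 exactly.
- Weights applied only after the fit, as the article describes: R is 1 plus a term set by how degree relates to outcome within the site. Site prevalence, where the arm effect lies, has been divided out.

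**Algebra of a fit that spans both arms.** With pair in the model and arm left out, fitted and observed totals agree within each pair. Ignoring covariates, the expected prevalence is (0.41 + 0.28)/2 = 0.345. The ratios are 0.41/0.345 = 1.19 and 0.28/0.345 = 0.81, and 0.81/1.19 returns 0.68.

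**Simulation.** 300 trials, k_m = 0.18, 1/degree weights applied after the fit, and Step 2 by linear regression on arm, baseline and pair (14 − 9 = 5 residual degrees of freedom). Assumed: log-normal degree with log-SD 0.7 and modest age and education effects. The prevalence ratio is the ratio of geometric mean residuals by arm; the true value is 0.28/0.41 = 0.683.

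| Step 1 model | Mean residual, intervention / comparison | Prevalence ratio | Null rejected |
|---|---|---|---|
| One per site (as written) | 1.002 / 1.001 | 1.000 | 3% |
| One across all sites, with pair | 0.814 / 1.187 | 0.685 | 84% |
| One per pair | 0.817 / 1.183 | 0.689 | 83% |
| None (unadjusted, RDS-weighted) | – | 0.683 | 82% |

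In the per-site version the lowest and highest residuals in a trial averaged 0.86 and 1.15. This is weighting noise, equal in the two arms.

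**Sensitivity to assumptions.**
- Two other simulations of the same design gave 0.999 with 5.5% rejection and 0.999 with 4.7% for the per-site model. One pooled model gave 0.69 with 81% and 0.69 with 77%.
- If women with the outcome have higher degree (assumed log shift 0.3), per-site residuals centre at 0.805 (intervention) and 0.836 (comparison). The per-site prevalence ratio is 0.96 with 11% rejection, against 0.665 with 84% for the pooled model.

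**Pair inside one site.** A design matrix with an intercept, a constant pair value and one covariate has rank 2 of 3, so the pair coefficient is not estimable.

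**The case against.** The strongest reply is that nobody would run this. Pair cannot be fitted within a site, the next sentence speaks of one model in the singular, and the article names the Hayes and Moulton method, whose model spans clusters. On that view 'for each site' is a drafting slip. A per-site analysis would also show itself through inestimable pair terms and 14 residuals scattered around a common value, and the planned unadjusted analysis would still show an effect.

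Much of this stands. A pooled model is the likely intent, and the unadjusted sensitivity analysis would retain the effect. Two limits on the criticism also stand. The residuals equal 1 exactly only without weights or with the same weights in the fit; when degree is related to outcome they shift away from 1, though by similar amounts in both arms. And pooling all 14 sites is not the only remedy, since one model per pair works about as well. The requirement is a model that covers both arms.

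None of this makes the stated primary rule correct. The article presents itself as reporting the analysis plan, so this is a wrong statement and not a detail left to another document. If the contradiction is resolved after endline data are seen, the choice is between a null and a non-null primary result.

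**Conclusion.** The concern holds for the text as written. Fitting Step 1 separately in each site removes the intervention effect from the primary analysis. Under the plan's own 41% versus 28%, the prevalence ratio moves from about 0.69 to about 1.00, and the chance of detecting the effect falls from roughly 77–84% to 3–5.5%. If degree is related to outcome, the ratio is about 0.96 and the effect is still essentially lost.

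The rejection rates depend on assumed degree distributions, covariate effects and between-site variation. The loss of the site's own prevalence from the residual does not; it follows from the score equation. The wording is probably a slip, but it sits in the one step that determines the trial's main conclusion, so it must be corrected.

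**What to change.** Replace the Step 1 model sentence with wording to this effect: *One logistic regression will be fitted to the endline data from all 14 sites combined, with age, education and six pair indicators as covariates and without study arm. Predicted values from this model will be weighted by inverse degree and summarised for each site.* Step 2 can stay as it is, though it would help to name the arm term in its regression.

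Using the RDS-2 weights (normalised within site) in the Step 1 fit as well would put expected and observed summaries on the same scale. This is optional: the pooled estimate was 0.690 with or without it.

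The cost is one sentence, changed before the endline data are analysed, plus a check that the analysis code fits the same model. No new data and no site work are needed.
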